### Use of Study Findings

Baseline study and impact evaluation findings will initially be shared with the government of UP, through Microsoft PowerPoint presentations and respective reports. The reports will also be shared with district officials of the 4 program districts for their review and consideration. Using data from baseline and end line surveys, ARMMAN will also develop research briefs on specific themes and look for opportunities to share these findings at various forums. If possible, the findings will also be disseminated through publication in scientific and peer-reviewed journals as well as through presentations at professional meetings and conferences. Once impact evaluation findings are available, ARMMAN plans to host meetings with state government officials and academicians to share relevant research findings, which could have implications for program modification when planning scale-up in other districts or states.

## Results

The impact evaluation protocol and the protocols for 6 HRP conditions were vetted by the government of UP in May-June 2024. In the 2 intervention districts of Sambhal and Shravasti, in June-July 2024, implementation of listed interventions started in a phased manner, and these interventions will continue for 18 months (until March 2026), in collaboration with district health officials. By November 2024, in the 2 intervention districts, the following interventions had been introduced: (1) protocols on 6 HRP conditions; (2) training of ANMs, MOs, specialist gynecologists, staff nurses, and community health officers on these protocols; and (3) a digital learning tool and a WhatsApp-based support system for ANMs. Baseline data from system stakeholders and community data from recently delivered women were collected during June-October 2024. From November 2024 to October 2025, the listed interventions will continue in the 2 intervention districts, and baseline data from both arms are being analyzed. By November 2024, all the ANMs, MOs, specialist gynecologists, staff nurses, and community health officers of 2 intervention districts were trained on 6 HRP protocols, the learning app for ANMs on the 6 HRPs, and the WhatsApp support system for real-time clarification of doubts by the ANMs (tech plus touch approach) was also introduced. The tracking and data integration system for improved tracking of the HRPs by health facilities at different levels of public health care system is yet to be introduced.

The proposed interventions, designed, developed, implemented, and evaluated using a tech plus touch approach, will capacitate HWs at different levels to make early diagnosis of the HRPs and provide protocol-based management of the diagnosed condition. The findings of the study will identify issues that require need-based planning to ensure quality ANC, delivery, and HRP care services by public health care system, and particularly the ANMs and MOs, who work at the grassroots. At the policy level, findings of the study will provide cues on facilitators and barriers to pregnancy care services at the block and district level, for necessary corrections. The study intends to make an important contribution by evaluating the usefulness and effectiveness of the proposed program and suggesting further improvements or modifications when scaled up across the entire state of UP, a region that is larger than many European countries.

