## Abstract

**Background:**

In India, 20%‐30% of pregnancies are high-risk, contributing to 75% of perinatal mortality and morbidity. An effective approach to reduce this mortality and morbidity is early identification, effective management, and timely referral of high-risk pregnancies (HRPs). The Integrated High-Risk Pregnancy Tracking and Management program aims to enhance the capacity of auxiliary nurse midwives (ANMs), medical officers (MOs), and specialist gynecologists by (1) providing algorithmic, color-coded, detailed yet simple HRP protocols, customized for each role; (2) offering live training; (3) delivering digital training and handholding; and (4) tracking management details for HRPs. Equipping health workers (HWs) with these interventions supports early identification, effective management, and timely referral of HRPs, ultimately improving primary care and enhancing satisfaction of mothers with HRPs. These interventions are implemented in the intervention arm for over 18 months. During this time, HWs of intervention and control arms will continue to receive routine training through state and national programs, and pregnant women of both arms have access to standard maternity services.

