Finally, HRP-specific data are linked with the state’s monitoring system to improve tracking and decision-making across different levels of the public health care system. This digital tracking system functions as a real-time data collection and decision-support tool integrated with the state’s HRP monitoring platform (Reproductive and Child Health [RCH] portal). It captures the management and referral journey of women with HRP conditions from anywhere in the state. The tracking app also guides HWs in recording relevant signs, symptoms, and diagnostic interventions, thereby ensuring that appropriate care is provided at every stage of management and referral for women with HRP conditions.

Our interventions are human-centric and user-focused, incorporating facility-specific actions tailored to the needs and responsibilities of each cadre within the health care system. The vision of the IHRPTM program is to improve the functioning of the public primary health care system and achieve a sustained reduction in irrational, delayed, and complicated referrals to higher-level facilities. This will ensure HSCs and PHCs manage mild to moderate HRPs, while only serious cases are referred to higher facilities. In turn, this reduces the burden on secondary and tertiary facilities, thereby improving the functioning of the 3 tiers of public health care system.

Thus, our innovative “tech plus touch model” leverages the existing public health care system to strengthen the capacity of HWs to manage HRPs, thereby facilitating scalability across districts or states. This approach includes an inbuilt sustainability model, as the IHRPTM program is integrated within the existing public health care system, without creating a parallel structure that would be resource intensive in terms of human and financial capital. Ultimately, a capacitated health care system and its stakeholders will create demand among mothers with HRPs for timely and appropriate care.

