While designing the impact evaluation of the UP pilot, the following contextual variations in the scale of direct beneficiaries were considered. The program engaged ANMs (>400 in UP vs >9000 in Telangana and >15,000 in AP), MOs (>100 in UP vs >1000 in Telangana and >1800 in AP), and specialists (>10 in UP vs >400 in Telangana and >500 in AP). Indirect beneficiaries also varied substantially, with approximately 60,000 pregnancies per year in UP compared with 700,000 in Telangana and 900,000 in AP, translating to roughly 18,000 HRPs per year in UP versus 200,000 in Telangana and 300,000 in AP. Training timelines also differed, while training all ANMs on 6 phase-1 protocols required approximately 1 year in Telangana and 9 months in AP, >400 ANMs in UP were trained in just a few days. Moreover, digital interventions were introduced within 2-3 months of program initiation in UP, compared with more than 3 years in Telangana and 1 year in AP, as these digital interventions were still evolving when implementation began in Telangana.

Thus, considering UP’s comparative advantage over Telangana and AP, sufficient number of direct and indirect beneficiaries, the rapid introduction of all interventions in quick succession, and additional scope for keeping a control arm, the UP impact evaluation design is expected to provide generalizable evidence on the program’s impact, even with its shorter duration (18 months) and smaller scale (2 intervention districts and 3 HRP protocols). In UP, the impact evaluation will be confined to the following 3 HRP conditions: anemia (moderate and severe), PIH, and APH.

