### Duration of Interventions and Justification for Creating a Usual Care Arm

In 2 intervention districts, the IHRPTM program will be implemented district-wide for 18 months, starting June-July 2024 and ending February-March 2026. The 18-month duration is necessary, as the introduction of different interventions in both the intervention districts requires 3‐6-month time. Also, for converting system level changes into outcomes is a time-consuming process [35]. Given the relatively short implementation period, we are not proposing a midline evaluation. However, the uptake, quality, and coverage of interventions will be continuously monitored through a robust monitoring system. Dipstick studies will be conducted depending upon the need. Any mid-course corrections will be based on findings from the baseline, monitoring data, and dipstick studies.

In the usual care arm, HWs will receive routine capacity-building sessions conducted by the state and the national governments. Pregnant women in both arms will have access to antepartum, intrapartum, and postpartum care programs provided by the state and the national governments. It implies that while general system strengthening interventions are provided in both the arms, the IHRPTM interventions are the only additional interventions confined to the intervention arm. At the community level, the IHRPTM program does not directly work with pregnant women in either arm. The control arm was included to isolate the effect of the IHRPTM interventions from the general system strengthening activities and to assess whether IHRPTM interventions had any incremental effect or value addition beyond what general system strengthening interventions alone can achieve. Thus, this study design ensures ethical equity while also allowing us to isolate the incremental effect of the IHRPTM program interventions by comparing changes in outcomes that go beyond improvements expected from broader system strengthening efforts.

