### Conclusions

The study will test the hypothesis of whether an integrated, comprehensive, system-driven intervention for improved identification, tracking, and end-to-end management of HRPs is feasible in geographies with poor maternal outcomes or not. At the community level, the study will provide insights on the role of sociodemographic, as well as ANC and delivery factors, that influence HRP management and referral practices. This trial will provide valuable insights into the feasibility and effectiveness of the program, at system and community levels, in low-resource settings like UP. If successful, these insights can feed into capacitating HWs, at scale, in all the districts on diagnosis and management of HRPs, with significant potential for improving maternal and neonatal outcomes of the state. We will also explore the options for scaling the program to include conditions beyond the 6 HRPs in other districts of UP.

For this study, the Transparent Reporting of Evaluations with Nonrandomized Designs (TREND) statement was followed [46] to ensure transparent and comprehensive reporting (Multimedia Appendix 8). Our protocol adheres to around 20 of the 23 items in the TREND checklist.

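### Tracking is counted among the interventions run for over 18 months, but the Results say it has not been introduced, so the evaluation estimates the effect of a narrower or partly delivered package

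*Protocol article*

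**What the plan says.** The Abstract (Background) numbers four programme components, the last being "4) tracking management details for HRPs", and continues: "These interventions are implemented in the intervention arm for over 18 months". The Methods section on the duration of interventions states that "the IHRPTM program will be implemented district-wide for 18 months, starting June-July 2024 and ending February-March 2026", and allows 3-6 months for bringing the different interventions in.

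Key Interventions of the Program describes tracking as a real-time data collection and decision-support tool tied to the state portal. It is presented as part of care, because it guides health workers in what to record. The theory of change has the tracking app supplementing training and the other digital tools.

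The Rationale for the Study (Overview) gives several reasons why a pilot of this length and size should yield generalizable evidence. One is "the rapid introduction of all interventions in quick succession".

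The Results section lists what was in place by November 2024: the six protocols, staff training, the learning app and the WhatsApp helpline. It then says that the system for better tracking of high-risk pregnancies "by health facilities at different levels of public health care system is yet to be introduced". No launch date is given there or elsewhere. The closing Conclusions still say the study will test whether an "integrated, comprehensive, system-driven intervention for improved identification, tracking, and end-to-end management of HRPs is feasible".

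**The concern.** The Abstract and the Rationale describe a full package delivered promptly and for the whole period. The Results describe a package with one named component missing. Both cannot be right, and the Rationale uses the full-package version as a premise for its claim of generalizability.

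Data Analysis applies DiD to the programme interventions as a whole, and the pilot is meant to inform extension to all 75 districts. If the article is left as written, a positive or null result would be read as a verdict on an integrated programme that includes tracking, although tracking may have been absent or live only briefly. The limitations in the Discussion do not mention this.

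**Working it through.** **Inputs**
- Programme period: June-July 2024 to February-March 2026, called 18 months (Methods, duration section; Results gives until March 2026).
- Introduction period: 3-6 months (same Methods section).
- Tracking status: not introduced, undated. The nearest dated statements in Results are November 2024 (components in place) and November 2024 to October 2025 (interventions continuing).
- End line respondents: women who gave birth in the past year (Community-Level Data Collection).

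**1. The plan's own 18 months.** The difference in months is 19 at the shortest (July 2024 to February 2026) and 21 at the longest (June 2024 to March 2026). The 18 months therefore has to be read as approximate, or as the time left after part of the phase-in.

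**2. Does the phase-in cover the gap?** Three to six months from June-July 2024 ends between September 2024 and January 2025. For a component to run 18 full months to the end of March 2026, it must be live by 1 October 2024. Tracking is not among the components in place by November 2024, so it misses 18 months even on the most favourable reading of the status date.

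**3. Longest possible tracking exposure** (calendar months, counted inclusively)
- Live from December 2024: 15 months to February 2026, 16 to March 2026.
- Live from November 2025: 4 months to February 2026, 5 to March 2026.
- Never launched: 0.

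**4. Share of an end line respondent's pregnancy with tracking live.** The assumptions are a 9-month pregnancy, deliveries uniform from 1 April 2025 to 31 March 2026, and end line at the end of March 2026. The launch dates are illustrative. For a delivery x months after launch, exposure is min(9, max(0, x)) months. Its average over the 12-month window, divided by 9, is the mean share.
- Launch 1 December 2024: x runs from 4 to 16. Mean = [(9² − 4²)/2 + 9 × 7]/12 = 95.5/12 = 7.96 months; share 88%. Whole pregnancy covered: 7/12 = 58%.
- Launch 1 May 2025: x runs from −1 to 11. Mean = [9²/2 + 9 × 2]/12 = 58.5/12 = 4.88 months; share 54%. Whole pregnancy covered: 2/12 = 17%.
- Launch 1 November 2025: x runs from −7 to 5. Mean = (5²/2)/12 = 12.5/12 = 1.04 months; share 12%. Whole pregnancy covered: none. Any coverage: 5/12 = 42%.
- Never launched: 0%.

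These shares are upper limits on real exposure. They count time with the tool live, not use of it, and Anticipated Challenges says 30%-44% of pregnant women in the state are reached partly or not at all by a public-sector programme.

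**The case against.** The strongest reply is that the gap is openly disclosed and does little harm. Results describes a phased start, and its status line holds only for the time of writing, so tracking may have gone live soon afterwards. The hypotheses in Hypothesis and Outcomes concern knowledge, skills, early diagnosis, management and antenatal care quality. None names tracking, and no listed outcome measures it. The theory of change ties the tracking app mainly to pathway data and dashboards, and attributes early diagnosis and management to training plus digital support. Much of this stands, and it is why the analysis itself is not undermined. It does not rescue the Rationale's premise or the Abstract's duration, which are wrong as written for this component.

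A reader might infer three stronger points, and the documents support none of them.

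- **That the DiD cannot support any conclusion.** It remains interpretable for the package as delivered, subject to its other assumptions. The sentence in Conclusions asks about feasibility, which DiD does not estimate in any case.
- **That the control arm is contaminated.** The tool is described thus: "It captures the management and referral journey of women with HRP conditions from anywhere in the state". That says where a woman's journey can be recorded. Nothing deploys the tool to workers in Gonda or Budaun, so no contradiction is shown with the statement that "the IHRPTM interventions are the only additional interventions confined to the intervention arm". Because the tool is linked to the state portal, who has access is an open question.
- **That tracking will have only 4-5 months.** This depends on one assumed launch date; the documents give none, and the range above is wide.

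**Conclusion.** The article contradicts itself on whether the full package was introduced. On any reading of the status date, tracking falls short of 18 months by March 2026: at most about 15-16 months, possibly 4-5, possibly none. Mean coverage of end line pregnancies by tracking runs from about 88% through 12% to 0%, given the pregnancy length, uniform deliveries, end line date and launch dates assumed above.

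The DiD estimate is therefore the effect of protocols, training, learning app and helpline, with tracking added only for the time it was live. This limits what the trial can conclude about an integrated programme and what it can say for scale-up. It does not invalidate the comparison.

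**What to change.** Reconcile the Abstract, the Rationale, the Results and the Conclusions on this component:

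1. Define the evaluated package as the components live in the intervention districts during the end line look-back, and state when tracking went live, if it did.
2. Replace the Rationale's premise that all interventions came in quickly with a statement of which ones did, and qualify the Abstract's duration in the same way.
3. Do not credit tracking in the conclusion or the scale-up claim unless it was live for the look-back period.
4. State in the Methods duration section whether health workers in the control districts can use the tool. This settles an open point and does not correct a shown error.

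The cost is a few sentences. Design, sample and analysis stay as they are, and no change to the tool's launch or access is needed. The downside is a narrower claim, with tracking left for later evaluation if it was absent or late.

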## Discussion

### Overview

One of the major strengths of this study is that this study is being implemented in partnership with state and district health departments. Through our multicomponent interventions, the capacity of public health care system stakeholders (ANMs, MOs, and specialists) is being built to diagnose and manage HRP conditions at their respective facilities. If ANMs and MOs manage HRPs at their level, there will be a reduction in unnecessary or late referrals to tertiary or higher-level facilities, allowing these facilities to concentrate mainly on the most critical cases. The study will establish a robust system for not only managing HRPs but for ensuring quality ANC services and continuum of care in geographies with poor maternal outcomes (Table 1). If the program is successful in these areas, it will pave the way for future implementation efforts in other states.

The proposed study anticipates a few limitations, such as delays in getting permissions to collect data from ANM, MOs, specialists, and RDW from the 2 control districts. In intervention districts, many MOs have recently joined the service, and their focus is on preparing for higher studies. Therefore, they may not be very keen to participate in this program. Also, if they get admission in higher studies, they will leave the service, and refilling the position may take time. We are also concerned about the support for the program from system stakeholders who are nearing retirement and working on a contractual basis. The end line qualitative results, particularly from the 2 intervention districts, might be influenced by social desirability bias, as by then, the majority of the system stakeholders will be aware of the purpose of the program and its objectives. To minimize the social desirability bias, we will do data collection methods triangulation and information triangulation (collecting same data from multiple question formats). To minimize the bias, we will also triangulate both qualitative and quantitative data, wherever feasible. Frequent transfers of district and state officials may also create hurdles in the timely implementation of interventions and getting approvals for implementing interventions on the ground.

### Conclusions

The study will test the hypothesis of whether an integrated, comprehensive, system-driven intervention for improved identification, tracking, and end-to-end management of HRPs is feasible in geographies with poor maternal outcomes or not. At the community level, the study will provide insights on the role of sociodemographic, as well as ANC and delivery factors, that influence HRP management and referral practices. This trial will provide valuable insights into the feasibility and effectiveness of the program, at system and community levels, in low-resource settings like UP. If successful, these insights can feed into capacitating HWs, at scale, in all the districts on diagnosis and management of HRPs, with significant potential for improving maternal and neonatal outcomes of the state. We will also explore the options for scaling the program to include conditions beyond the 6 HRPs in other districts of UP.

For this study, the Transparent Reporting of Evaluations with Nonrandomized Designs (TREND) statement was followed [46] to ensure transparent and comprehensive reporting (Multimedia Appendix 8). Our protocol adheres to around 20 of the 23 items in the TREND checklist.
